Resting-state baselines will be collected preexposure and postexposure (T0 and T1) with 2-minute eyes-open (fixation cross) and 2-minute eyes-closed recordings while participants sit quietly, instructed to stay relaxed, minimize blinking, and avoid large movements. During the 20-minute nature or VR exposure, EEG will be recorded continuously while participants remain seated; they will be reminded that they may pause or terminate the session if they experience discomfort, and any early termination will be documented and treated as dropout for EEG analysis. Evidence from previous VR-EEG studies [83] and from our own pilot testing indicates that simultaneous use of the FLEX cap and the VR headset is safe and allows reliable signal acquisition. Nevertheless, because VR head-mounted display padding can occasionally impinge on frontal or frontopolar sites, headset fitting will follow a predefined substitution protocol: if AF3/AF4 are partially obstructed, frontal alpha asymmetry will be computed from the canonical F3/F4 pair; if Fp1/Fp2 cannot be used, priority will be given to maintaining midline integrity at Fz. For any substituted electrodes, 3D electrode positions will be digitized to allow offline correction of spatial shifts, and the midline chain Fz-Cz-Pz-Oz will be preserved in all participants for core spectral and ERP analyses.

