#### Power

Sample size estimation focused on the primary mechanistic outcomes of the study, namely preexposure to postexposure changes in EEG alpha power and performance on the 2 cognitive tasks as a function of diagnostic group (ADHD vs neurotypical) and exposure condition (real nature vs VR nature). Power calculations were conducted in G*Power (version 3.1; Heinrich Heine University Düsseldorf), using a 2 × 2 × 2 mixed-model ANOVA (group × condition × time: preexposure vs postexposure). Pilot data from a comparable ADHD sample [84] indicated a pre-to-post change in alpha amplitude of 6.93 μV (SD 2.04) at baseline and 7.88 μV (SD 1.83) postintervention, corresponding to a Cohen *d* of 0.49 (moderate effect size) for the within-subject contrast. Assuming a correlation of 0.5 among repeated measures, this maps onto a repeated-measures ANOVA effect size in the moderate range.

Using a 2-tailed α of .05 and desired power of 0.80, the required total sample size was calculated to be 64 to 72 participants (approximately 16 to 18 per cell in the 2 × 2 design) to detect effects in this range on the primary EEG outcome. To accommodate potential attrition and data loss (eg, unusable EEG recordings), a 20% buffer was applied, resulting in a final recruitment target of 80 participants (n=20 per subgroup). This sample size is expected to provide adequate statistical power to detect moderate pre-post effects and group × condition interactions on alpha power and core cognitive outcomes.

Secondary and exploratory analyses (eg, EMA trajectories, dimensional ASRS scores, and follow-up data) will be modeled using linear mixed-effects approaches in the same sample. These models are intended to characterize patterns of change over time and symptom-related gradients in responsiveness; findings from these analyses will therefore be interpreted with appropriate attention to effect sizes and precision estimates rather than relying solely on hypothesis-testing thresholds. The planned sample provides ≥80% power to detect moderate pre-post changes in alpha power for the primary group × condition × time effect in the planned linear mixed-effects analysis. Analyses of higher-order interactions and secondary outcomes (eg, EMA trajectories) will be considered exploratory and interpreted cautiously.

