#### Statistical Methods

All analyses will follow an intention-to-treat approach and will be conducted using R (R Foundation for Statistical Computing). Statistical tests will be 2-tailed with a significance level of α=.05. Descriptive statistics will summarize sample characteristics. Baseline group differences will be assessed using Pearson chi-square tests for categorical variables and independent-samples *t* tests (or nonparametric equivalents) for continuous variables. Any variables showing systematic baseline imbalance will be considered as covariates in sensitivity analyses.

To evaluate the primary outcomes—changes from preexposure (T0) to immediate postexposure (T1) in EEG alpha power, cognitive performance (Meta Mind and Star Racer), and ASRS, we will implement linear mixed-effects models (LMMs) using the *lme4* package. Fixed effects will include exposure condition (real vs VR nature), diagnostic group (ADHD vs neurotypical), time (T0 vs T1, with T9 added where relevant to examine short-term maintenance), and their interactions. Participant will be entered as a random intercept; random slopes for time will be added where supported by convergence and model fit. The primary contrasts of interest are: (1) group × condition × time for alpha power in predefined frontal and parietal regions of interest, and (2) condition × time and group × time interactions for cognitive and ASRS outcomes.

For EEG data, log-transformed alpha power (8-13 Hz) will be averaged within each region of interest and exposure phase. Within-subject change scores (T1-T0, and T9-T0 where applicable) will be analyzed in the LMM framework described above. Exploratory time-resolved effects across the 20-minute exposure will be examined using cluster-based permutation tests on epoch-wise alpha power, with family-wise error controlled at 0.05. Effect sizes will be reported as Cohen *d* for pairwise contrasts and partial eta squared (η^2^_p_) for omnibus tests.

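### The primary EEG analysis is specified in two inconsistent ways, and the version that can be fitted uses the T0 value inefficiently for the randomised contrasts

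*Protocol article*

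**What the plan says.** All references are to the Protocol article.

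- **Model (Statistical Methods).** The T0-to-T1 primary outcomes go into lme4 models with condition, group, time and their interactions as fixed effects. On random effects: "Participant will be entered as a random intercept; random slopes for time will be added where supported by convergence and model fit". The primary EEG contrast is group × condition × time for alpha power. For cognition and ASRS the primary contrasts are condition × time and group × time.
- **EEG (same section, next paragraph).** Log alpha power is averaged within each region and exposure phase, and then: "Within-subject change scores (T1-T0, and T9-T0 where applicable) will be analyzed in the LMM framework described above".
- **EEG time points (EEG Recording and Preprocessing).** "Resting-state baselines will be collected preexposure and postexposure (T0 and T1"), plus continuous recording during the exposure. Procedures likewise describes EEG only for the exposure session. Neither section describes EEG at T9.
- **Covariates (Statistical Methods).** The T0 value is not a planned covariate. Only variables found to be imbalanced are considered, and only in sensitivity analyses.
- **Allocation (Procedures).** 1:1 permuted blocks within diagnostic stratum, with envelopes opened after baseline measures.
- **Power.** "Assuming a correlation of 0.5 among repeated measures", with 80 participants, 20 per cell.

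**The concern.** The sentence on change scores sends the analyst back to a model that change scores cannot enter. Differencing removes time, so the declared group × condition × time contrast becomes group × condition. It also leaves one row per participant per region, so the participant intercept has nothing to estimate. The T9-T0 term refers to EEG data that the protocol does not describe collecting. Someone must therefore decide later which specification of a primary outcome applies.

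The second issue is efficiency. Condition is randomised within each diagnostic group after T0, so T0 means are equal in expectation between conditions within a stratum. A model that subtracts the whole T0 value, instead of an estimated fraction of it, adds noise to the randomised comparison without removing any bias. The study has only 20 people per cell and a three-way primary EEG contrast, so that loss matters.

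**Working it through.** **1. The protocol's own figures.** Inputs (Power section): "6.93 μV (SD 2.04) at baseline and 7.88 μV (SD 1.83) postintervention".

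- d = (7.88 − 6.93) / √[(2.04² + 1.83²)/2] = 0.95 / 1.938 = 0.490, so the stated 0.49 reproduces.
- The stated requirement of 64 to 72 did not reproduce. With f = 0.49/2 = 0.245, two measurements and r = 0.5, the noncentral F calculation gives 36 (within-subject effect, or a two-group interaction) or 52 (four-group interaction, 3 df). The steps below do not depend on it.

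**2. Which specifications can be fitted.** lme4 was run on simulated data with N = 80.

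- Change score on group × condition with a participant intercept: stops, because the number of grouping levels must be less than the number of observations. The likelihood depends only on the sum of the two variances.
- T0/T1 rows with group × condition × time and a participant intercept: fits. The three-way estimate is 0.191 (SE 0.454), identical to ordinary least squares on change scores (0.191, SE 0.454).
- The same rows with a random time slope added: stops (160 observations, 160 random effects).
- Change scores from two regions stacked in one model: fits, but the section does not list region as a model factor.

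**3. Variance of the randomised contrasts.** Per-participant variance, with a common SD of σ at T0 and T1:

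- Change score: 2(1 − r)σ²; at r = 0.5 this is 1.00σ².
- T0-adjusted: (1 − r²)σ²; at r = 0.5 this is 0.75σ².
- Ratio: (1 + r)/2, so the cut is 1 − (1 + r)/2.
- With the pilot SDs at r = 0.5: change 2.04² + 1.83² − 2(0.5)(2.04)(1.83) = 3.777; adjusted 1.83² × 0.75 = 2.512; ratio 0.665, a cut of 33%.
- Simulation (20,000 trials of 80, equal SDs, r = 0.5): ratio 0.762 for the group × condition contrast, after the cost of estimating the slope.

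**4. Power for the EEG three-way contrast.** SE = SD × √(16/N), where SD is that of the change score or the T0-adjusted residual; difference 0.49 SD, N = 80, two-sided 5%. At r = 0.5:

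- Change score: SE = √(16/80) = 0.447.
- T0-adjusted: SE = 0.447 × √0.75 = 0.387.

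| r | Variance cut (equal SDs) | Power, change score | Power, T0-adjusted |
|---|---|---|---|
| 0.3 | 35% | 0.150 | 0.205 |
| 0.5 | 25% | 0.191 | 0.239 |
| 0.7 | 15% | 0.287 | 0.328 |
| 0.9 | 5% | 0.677 | 0.699 |

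At r = 0.5, 80% power would need about 528 participants with change scores and 396 with T0 adjustment.

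**5. The non-randomised contrast.** Suppose ADHD and control differ by −0.5 SD at T0 and change equally. The T0-adjusted group effect is then −0.5 − 0.5 × (−0.5) = −0.25 SD, although the true difference in change is zero. Simulation gave −0.249 with adjustment and 0.001 on change scores.

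**The case against.** Several stronger readings are tempting, and the documents do not support them.

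- **That the primary EEG analysis cannot be fitted.** The T0/T1 model in the paragraph before is fittable and carries the declared contrast. Only the change-score wording fails, and stacking regions would rescue even that. The defect is inconsistent specification.
- **That the random slope and T9-T0 are firm commitments to the impossible.** The slope is added only if convergence and fit support it, and T9 data exist for ASRS and cognition. The T9-T0 term carries its own qualifier. It remains loose wording in an EEG paragraph.
- **That T0 is thrown away.** It is used, with a coefficient of 1.
- **That adjustment always saves a quarter, at no cost.** The saving depends on r, which the protocol assumes and does not estimate. It is near-free only for randomised contrasts.
- **That power improves substantially.** At 0.49 SD and N = 80, condition × time would go from 0.581 to 0.705. But that is a primary contrast for cognition and ASRS, not EEG, and the calculation treats the EEG quantity "corresponding to a Cohen *d* of 0.49 (moderate effect size) for the within-subject contrast" as if it were a difference between conditions.

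It can also be said that the change-based test is valid, that the protocol defines the EEG outcome as a change, and that exact formulae may stand in the preregistered analysis plan, which is not shown. The validity point stands: this is a loss of precision, not bias. The last point does not dispose of the matter, because the article itself states two specifications that conflict.

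**Conclusion.** The point holds as an inconsistency to be reconciled and a worthwhile gain in precision. Taken literally, the change-score sentence contradicts the model it refers to, and no EEG at T9 is described. The fittable T0/T1 model equals change-score analysis when data are complete, so it is less efficient than it need be for contrasts randomised within stratum.

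The size is a 25% lower variance at r = 0.5 with equal SDs (33% with the pilot SDs), ranging from 35% to 5% as r goes from 0.3 to 0.9. This rests on the assumed correlation and on randomisation within diagnosis. It does not rescue the stated 80% power for the three-way EEG effect, which stays near 24% at 0.49 SD, N = 80 and r = 0.5.

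**What to change.** 1. Delete the change-score sentence and the T9-T0 term for EEG.
2. For the randomised contrasts (condition × time and group × condition × time), name one model:
   - T1 regressed on T0, group, condition and group × condition, with no random effect; or
   - a T0/T1 mixed model with T0 means constrained equal between conditions within each diagnostic group but free between groups.
3. Estimate the non-randomised group × time contrasts on unadjusted change. The two options in item 2 are not interchangeable here: the group coefficient from the T1-on-T0 regression answers a different question and should not be reported as group × time.

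The cost is analysis wording and one degree of freedom. T0 is already collected, and neither the sample size nor any procedure changes. The change should be made before the analysts are unblinded.

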### Procedures

Participant enrollment will be conducted through a face-to-face clinical interview with a trained psychologist or psychiatrist to confirm the diagnosis of ADHD and assess potential comorbidities based on *DSM-5* (*Diagnostic and Statistical Manual of Mental Disorders, Fifth Edition*) criteria.

Following informed consent and completion of baseline assessments, participants will be stratified by diagnostic status (ADHD vs neurotypical control). Within each stratum, the random allocation sequence will be generated by an independent research coordinator (not involved in recruitment or outcome assessment) using computer-generated permuted blocks of variable size with a 1:1 allocation ratio. This stratified block design ensures balanced group sizes over time and equal distribution of diagnostic groups across conditions.

The allocation sequence will be implemented using sequentially numbered, opaque, sealed envelopes prepared in advance by the independent research coordinator. Treating clinicians or research assistants will enroll participants and open the next envelope only after baseline measures are completed, ensuring that upcoming assignments remain concealed from both participants and enrollment staff. Due to the nature of the intervention condition, blinding of participants and experimenters is not feasible; however, data analysts will remain blinded to group allocation and condition labels until the primary analyses are completed to minimize bias during statistical analysis.

As illustrated in Figure 1, cognitive and emotional assessments will be administered at 10 time points: preexposure (T0), immediately postexposure (T1), and weekly over an 8-week follow-up period (T2-T9). These assessments will be completed online within the study platform. ADHD-specific assessments will be conducted at 3 time points: T0, T1, and the final follow-up (T9). EEG data will be recorded continuously during the exposure session to capture real-time brain activity in response to the environmental condition.

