### Follow-Up Assessments

Existing work on nature exposure largely falls into 2 patterns: single-session studies that examine immediate effects and multiweek intervention programs involving repeated exposure (eg, weekly 45-minute walks in nature), with follow-up data suggesting that some benefits are no longer detectable at 1-month follow-up [64]. Against this background, this study includes an extended follow-up after a single 20-minute exposure to real or VR-simulated nature, delivered via an online survey platform that sends automatic weekly reminders before each assessment to support retention and minimize participant burden.

Beyond the immediate postexposure assessment, participants complete weekly online follow-ups over an 8-week period. The primary rationale for these repeated assessments is to characterize how any acute changes in cognition and mood observed at T1 decay over time. This design allows us to estimate the short-term time course of attenuation and to explore whether the pattern of change differs between exposure modalities and between individuals with different neurocognitive profiles, including varying levels of ADHD symptoms. Such information may help to inform the scheduling and dosing of future nature-based interventions.

In addition, the extended 8-week window provides an opportunity to examine more gradual shifts in lifestyle and nature relatedness. At baseline and at follow-up, we record the frequency and duration of participants’ additional contact with real outdoor nature and VR-based nature experiences, as well as repeated measures of nature connectedness using the Nature Connection Index (NCI) [65]. These data will be used descriptively and in exploratory analyses to assess whether a single experimental session has any downstream impact on everyday nature exposure or perceived connection to nature while also helping to account for ongoing environmental input when interpreting long-term trajectories.

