Secondary outcomes include trajectories of emotional well-being assessed via weekly EMA, clinical functioning in the group with ADHD (ACOS-Self), quality of life (AAQoL), and nature connectedness (NCI). EMA scores over T0-T9 will be modeled with LMMs including fixed effects for time (treated as a continuous or categorical variable depending on fit), condition, group, and their interactions, with random intercepts for participants. ACOS-Self, AAQoL, and NCI change from T0 to T9 will be analyzed using separate LMMs with fixed effects for group, condition, and their interaction. Self-reported real-world nature and VR exposure during follow-up will be explored as time-varying covariates in additional models to probe their contribution to decay or maintenance of effects.

To incorporate a dimensional perspective, *z*-scored ASRS total and subscale scores will be included as continuous predictors in a restricted set of prespecified models [85] (eg, ASRS × condition × time interactions for alpha power and cognitive outcomes). These analyses will test whether attentional trait variation predicts sensitivity to environmental exposure across the full sample, without overparameterizing models.

Multiple-comparison control will be applied at the level of outcome families: EEG (regions of interest and key contrasts), cognitive tasks (Meta Mind and Star Racer indices), EMA trajectories, and clinical measures. Within each family, *P* values will be adjusted using false discovery rate procedures; unadjusted and adjusted values will both be reported.

Model assumptions (normality of residuals, homoscedasticity, and, where relevant, sphericity) will be checked using diagnostic plots and formal tests. If assumptions are violated, transformations or robust alternatives will be considered. Missing data will primarily be handled within the mixed-model framework under a missing-at-random assumption. In addition, sensitivity analyses will be conducted using multiple imputation and complete-case subsets (participants with data at least up to T1 and T9) to examine the impact of attrition on key inferences.

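### The exploratory EMA trajectory model has random intercepts only and leaves pre-exposure T0 inside a time effect whose coding is chosen by fit; fitted linearly, it would understate decay and probably overstate precision

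*Protocol article*

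**What the plan says.** The secondary-outcome paragraph of Statistical Methods states that "EMA scores over T0-T9 will be modeled with LMMs including fixed effects for time", and continues with "condition, group, and their interactions, with random intercepts for participants". Time is to be "treated as a continuous or categorical variable depending on fit", and no other random effect is stated.

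For the primary models, the same section adds that "random slopes for time will be added where supported by convergence and model fit". The EMA paragraph has no such sentence and no term for serial correlation.

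Procedures gives ten occasions: T0 before exposure, T1 immediately after it, and T2 to T9 weekly. Follow-Up Assessments explains why they exist: "The primary rationale for these repeated assessments is to characterize how any acute changes in cognition and mood observed at T1 decay over time".

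The Power section calls EMA trajectories exploratory and asks that they be read through effect sizes and precision. Statistical Methods still computes P values for the EMA family and adjusts them for false discovery rate.

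**The concern.** There are two separate difficulties.

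**Target.** The question is what happens after T1. A single time effect over T0-T9 also contains the jump from T0 to T1. A straight line has to average a rise and a fall, so its slope is not the decay rate.

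**Covariance.** Random intercepts alone assume that all pairs of occasions are equally correlated and that people in the same cell share one trajectory. The protocol's own hypotheses point the other way: the Introduction anticipates a faster loss of gains at higher symptom levels, along a continuum. The EMA model carries diagnostic group but not ASRS, so symptom-related differences in decay within a group become unmodelled slope variation. Adjacent weekly mood scores are also likely to resemble each other more than distant ones.

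At stake are the two quantities the Power section says will carry the interpretation, effect size and precision. Follow-Up Assessments and the Discussion also expect the results to inform the scheduling and dose of later nature-based interventions.

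**Working it through.** The protocol gives no EMA slope, variance component or standard error, so there is no stated figure to reproduce. Inputs taken from it: ten occasions, 80 participants (40 per condition), two-sided α of 0.05. Everything else below is an assumption shown as a range.

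**1. Slope through T0-T9.** Take a gain of 1 unit at T1 that falls linearly to 0 at T9. The true decay slope is −1/8 = −0.125 per week. Scores are 0 at T0, then 1, 7/8, …, 0, with mean 0.45.

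- *Time in weeks* (0, 0, 1, …, 8; mean 3.6): Sxx = 204 − 10 × 3.6² = 74.4; Sxy = 10.5 − 10 × 3.6 × 0.45 = −5.7; slope = −5.7/74.4 = −0.077, which is 61% of −0.125.
- *Occasion number* (0 to 9; mean 4.5): Sxx = 82.5; Sxy = 15 − 10 × 4.5 × 0.45 = −5.25; slope = −0.064, which is 51%.
- *No decay at all* (0, then 1 throughout; weeks): Sxy = 36 − 10 × 3.6 × 0.9 = 3.6; slope = +0.048 per week, a rise where the true post-exposure slope is zero.
- *Exponential decay* (weeks), half-life 1, 2, 4 or 8 weeks: the line recovers 70%, 65%, 52% or 24% of the slope fitted to T1-T9.

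**2. Standard error of condition × time, linear time.** With balanced data, the random-intercept slope estimate equals within-person least squares. Set residual SD to 1.

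- *Slopes vary with SD τ.* True variance of a person's slope is (1 + τ²Sxx)/Sxx; the model reports about (1 + τ²Sxx/9)/Sxx. For τ = 0.10 by occasion number, τ²Sxx = 0.825, so true/model SE = √(1.825/1.092) = 1.29, and type I error = 2[1 − Φ(1.96/1.29)] = 0.13.
- *AR(1) errors with correlation ρ.* The same comparison uses the AR(1) covariance between occasions.

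| Assumption | True/model SE | Type I error |
|---|---|---|
| τ = 0, ρ = 0 | 1.00 | 0.05 |
| τ = 0.05 | 1.09 | 0.07 |
| τ = 0.10 | 1.29 | 0.13 |
| ρ = 0.3 | 1.28 | 0.125 |
| ρ = 0.5 | 1.52 | 0.20 |

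The table uses occasion number; time in weeks changes the type I errors by less than 0.01. Simulation with 4,000 runs per setting gave 0.127 for τ = 0.10, 0.122 for ρ = 0.3 and 0.201 for ρ = 0.5. Testing participants' own slopes, which lets slopes vary, gave 0.046 to 0.054 in every scenario simulated.

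**3. Categorical time.** There is no dilution, because T9 − T1 is contrasted directly. For τ = 0.10 or ρ of 0.3 to 0.5, true/model SE is 1.04 to 1.10 for T9 − T1 (reported SE too small) but 0.78 to 0.96 for T1 − T0 (too large). The simulated omnibus condition × time type I error is 0.05 to 0.07.

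**4. Would fit choose categorical time?** The criterion is not named; AIC is assumed here. With all interactions, categorical time uses 4 × 9 = 36 time parameters and linear time 4 × 1 = 4, a difference of 32. AIC then needs a likelihood-ratio statistic above 64. For the linear-decay profile in weeks, lack of fit to a line is 1.1625 − 5.7²/74.4 = 0.726 per squared unit of gain. With 80 people and a gain of δ residual SD, the expected statistic is about 32 + 80 × 0.726δ² = 32 + 58δ². It reaches 64 only at δ = √(32/58) ≈ 0.74. For smaller gains, AIC on the full model tends to keep the line. Comparing the codings with fewer interactions would favour categorical time sooner.

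**The case against.** A reader might infer that the reported standard errors are too small and the decay slope diluted whatever is fitted. The documents do not support that. Categorical time is one of the two options named; under it there is no dilution, and the T1 − T0 standard error errs in the opposite direction. Under linear time, the standard-error problem needs slope variation or serial correlation. Both are likely for weekly mood scores, but the protocol gives no figure for either, and with neither the type I error is 5%.

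The 51% figure needs T0 and T1, which bracket a 20-minute session, to be coded as far apart as two weekly visits. The 61% figure, with time in weeks, is the fairer one. Nor are these ten weekly scores: two belong to the session and eight are weekly.

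The protocol also plans assumption checks, including sphericity where relevant, and says robust alternatives will be considered. It is silent on EMA random slopes and does not forbid them. Covariance details are often left to a fuller analysis plan. Above all, the trajectories are labelled exploratory and no primary conclusion rests on them.

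A reader might further infer that the weekly cognitive scores go unanalysed, since the detailed cognitive model names only T0, T1 and T9. The Power section says that follow-up data will be modelled with mixed-effects methods, so that inference goes too far.

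Most of this stands and limits the size of the point. It does not remove it: the model is written down, it lacks a clause that its neighbour has, and choosing the coding by fit does not reliably protect the decay estimate. The general fallback names neither random slopes nor serial correlation, and false-discovery adjustment cannot repair P values that are too small to begin with.

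**Conclusion.** The point holds in conditional form, as a specification fixed badly and not as missing detail.

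- **If time is linear**, the T0-T9 slope is not the decay that the follow-up is meant to describe. This follows from the design alone; its size (61% in weeks, 51% by occasion number, a false rise with a persistent gain) depends on the assumed shape of the decay.
- **If, in addition, slopes vary or errors are serially correlated**, condition × time is tested at about 7-20% instead of 5%, for slope SD 0.05-0.10 residual SD per step or AR(1) 0.3-0.5. These inputs are assumptions.
- **If time is categorical**, only a smaller standard-error problem remains, and its direction differs by contrast.

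Severity is minor to moderate because the analysis is exploratory.

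**What to change.** Replace the choice by fit with a coding set in advance that separates the T0-T1 step from T1-T9. Suitable forms are T0 as a covariate with T1-T9 as outcomes, piecewise time (a post-exposure step plus a slope), or categorical time with the T1-T0 and T9-T1 contrasts named. Measure time in weeks since exposure.

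Add a random slope for time, as the primary models already allow, or AR(1) within-person errors, and use small-sample degrees of freedom. A fully unstructured covariance over T1-T9 is not advised: it has 9 × 10/2 = 45 parameters for at most 80 people.

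The cost is wording, before data collection begins. Intervals will be somewhat wider, and AR(1) errors need a package other than lme4. The random-slope option stays within lme4.
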